## Methods/design

This is a parallel 3-group, multicenter, prospective, randomized; single-blind (evaluator) controlled pilot trial, with a 4 month follow-up post-intervention. Patients diagnosed with bipolar disorder (BD) according to DSM −5 criteria for mild depression or subsyndromal depressive symptoms are assigned to one of the following 3 treatment groups: 1) psychopharmacological treatment *plus* Mindfulness Based Cognitive Therapy (MBCT); 2) psychopharmacological treatment *plus* a brief, structured group psychoeducation; 3) treatment as usual (TAU), defined as standard psychiatric care with standard pharmacologic treatment. After written informed consent is signed, patients meeting the inclusion criteria are randomized (2:2:1 ratio) through a Random Allocation Software. All three groups are assessed at baseline (t0), immediately after completing the program (t1; 8 weeks) and at follow-up six months after randomization. The assessments include the following variables: depression, manic and anxiety symptoms, general and social cognition, global functioning, BDNF, and other clinical variables. The evaluator who will collect the biomarkers and the clinical and psychometric data will be blind to allocation of treatment. The interrater variability between all researchers will be checked.

### Subjects

One hundred and forty bipolar out-patients with persistent mild/subsyndromal depressive symptoms will be recruited from Mental Health Centers as well as Private Psychiatric Clinics and Bipolar Patient Associations via announcements or physician referral. The study will be conducted in La Paz University Hospital (Madrid) and the Santiago Apóstol University Hospital (Vitoria).

### Inclusion criteria

1-Age: 18–60 years; 2 – BD type I or II, in clinical remission of acute mood episode at least in the three months prior to study; 3 - Having experienced an acute affective episode in the past 3 years, 4 - Having suffered at least two lifetime depressive episodes. 5- Monotherapy or combination with a mood stabilizer (lithium, valproate, carbamazepine or lamotrigine) at optimal doses (i.e., in serum levels within the therapeutic range: 0.6-1.2 mEq/L for lithium, 50–100 ug/mL for valproate, and 5–12 mcg/mL for carbamazepine), or quetiapine monotherapy or in combination with the aforementioned stabilizers, or any oral atypical antipsychotic in combination with an antidepressant; 6.- Hamilton Depression Rating Scale [HDRS]–17 [44] score ≥ 8 and ≤ 19 and Young Mania Rating Scale [YMRS; 49] score <8; 7 - Being able to understand and comply with the requirements of the trial, 8 - Written consent to participate in the study.

### Exclusion criteria

1. Any acute mood episode in the 12 weeks before the start of the trial. 2. Any current DSM −5 diagnosis different from bipolar disorder (including substance or alcohol use disorder at the time of study entry, except if it is under complete remission. Not applicable to nicotine or caffeine). 3. Risk of suicide or self/hetero aggressiveness. 4. Pregnancy. 5. Severe and unstable medical disease. 6. Patients who are currently receiving structured psychotherapy or structured group psychoeducation about bipolar disorder, or who have received structured psychoeducation in the past 5 years; 6. Patients who are treated with a different mood stabilizer than lithium, valproate, carbamazepine, lamotrigine, a classic antipsychotic or antidepressant monotherapy at the time of the randomization. 7. Treatment with a depot antipsychotic; 8. Participation in another clinical trial within 4 weeks prior to randomization. 9. Mental retardation.

### Withdrawal criteria

Express wish of the participant, unjustified absence from more than two group training sessions, appearance of suicidal ideation or psychotic symptoms, onset of acute manic or hypomanic episode, or need for psychiatric hospitalization from any cause.

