### Secondary endpoints

Changes in the global score of Young Mania Rating Scale (YMRS, [45]) from baseline (V0) to visit 1 (at the end of the 8 week intervention (v1)Changes in the score of Clinical Global Impression CGI-BP [46] from baseline (V0) to visit 1;Changes in the score of the Hamilton Rating Scale for Anxiety HAM-A [47] from baseline (V0) to visit 1;Cognitive changes: changes at the end of the intervention will be assessed with the following measures:sustained and selective attentionworking memory and executive functionsperception of the attitude of mindfulness (Five Facet Mindfulness Questionnaire FFMQ, [48]) in patients in the experimental groupscales of social cognitionFunctioning: changes in total scale score of the Functioning Assessment Short Test (FAST; [49]).The following clinical variables are also assessed:Recurrence, defined as the emergence of a new acute episode whether depressive, mixed, hypo or manic at any time throughout the study, according to DSM-5 clinical criteria or when the score on the HDRS scale is ≥ 20 (depressive episode) or the Young scale ( YMRS ≥ 8) (hypo/manic episode), or a change drug or hospitalization is needed.Plasma levels of BDNF: changes from baseline to visit 1 (end of intervention).

Twenty-four weeks after the start of intervention following measurements are assessed: changes in the overall score of the Hamilton Depression Rating Scale (HDRS [44]), Young Mania Rating Scale (YMRS, [45]) from baseline (V0 ) to week 24 (V2) , Hamilton anxiety Scale HAM- A [47], CGI [46], general cognitive functioning, social cognition, functioning and biomarkers (BDNF).

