### Intervention

MBCT program will be conducted in HULP by two experienced therapists with recognized expertise in Mindfulness based stress reduction (MBSR), MBCT and narrative psychotherapy. Both therapists will train two therapists from Vitoria with expertise in cognitive therapy and MBSR. The MBCT program consists of 8 weekly sessions of 90 minutes and will be performed in groups of approximately 10–15 patients. All therapy sessions will be audio recorded to be discussed and analyzed by the treatment team, in order to standardize the intervention. Treatment fidelity will be also assessed using the Mindfulness- based Cognitive Therapy Adherence Scale (MBCT-AS; [50]), which assesses the key constructs of MBCT during group sessions.

Psychoeducation program will be held in groups of 10 to 15 patients in 90-minute weekly sessions led by two therapists blind to the clinical and cognitive evaluation. The specific program of 8 sessions addresses disease awareness, adherence to treatment and early detection of prodromal symptoms. Homework will also be included. The program is based on the Psychoeducation Manual for Bipolar Disorder [51]. Attendance to at least 80% of the sessions of both interventions will be required to be considered complete.

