#### f) Biomarkers: serum analysis of BDNF

### Data analysis

An exploratory study of all collected variables identifies possible outliers and errors. The descriptive analyses of qualitative variables are expressed as frequencies and percentages and quantitative variables as mean, standard deviation, median and interquartile range. Analysis is performed by intention to treat. Comparison of qualitative variables between the intervention groups or between other factors of segmentation is by means of Chi 2 or Fisher ‘s exact test. For quantitative variables, the T-test, Mann -Whitney or Kruskal –Wallis and ANOVA are applied, depending on the normality of the variable (tested by Kolmogorov -Smirnov - Lilliefords). The change analyses along the track of the primary and secondary outcome variables are performed using a General Linear Model (ANOVA with repeated measures). Regression models are extracted to identify prognostic factors for the efficacy variables. The statistical package SPSS 18.0 is used in all tests and a bilateral level of p < 0.05 is considered statistically significant.

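### Intention to treat is not secured as written: withdrawal is not separated from the end of assessment, one withdrawal rule can act only in the group arms, and the named ANOVA needs every entered visit

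*Protocol article*

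**What the plan says.** All places are in the Protocol article.

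- **Withdrawal criteria.** Beside the participant's own wish, the list has "unjustified absence from more than two group training sessions, appearance of suicidal ideation or psychotic symptoms, onset of acute manic or hypomanic episode" and "need for psychiatric hospitalization from any cause". It is a single list. It does not say whether a listed event ends the intervention, the assessments, or both.
- **Data analysis.** "Analysis is performed by intention to treat". Change in the primary and secondary outcomes is "performed using a General Linear Model (ANOVA with repeated measures"), run in SPSS 18.0. Nothing is said about patients without a later visit.
- **Methods/design, opening paragraph.** The three groups are allocated 2:2:1 and assessed at baseline, week 8 and six months. Withdrawn patients are not mentioned.
- **Primary outcome measures.** The endpoint is HDRS change from V0 to week 8.
- **Secondary endpoints.** Recurrence counts "at any time throughout the study, according to DSM-5 clinical criteria", and alternatively by scale thresholds, a drug change or hospitalisation.
- **Aims.** The Abstract sets MBCT against psychoeducation. The last paragraph of Background adds standard clinical management to the objective.

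**The concern.** Three rules that the article itself fixes do not fit together. An intention-to-treat analysis needs outcome data on everyone randomised. A withdrawal list that includes missed sessions and clinical deterioration threatens those data for reasons tied to arm and to outcome. A classical repeated-measures ANOVA then leaves out any patient who lacks one of the visits entered. That last point is a property of the method and is not stated in the article.

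The absence rule is the part that is unequal by construction. MBCT and psychoeducation each have eight sessions and TAU has none. A patient who disengages can be withdrawn from a group arm, while an equally disengaged patient in TAU stays in. If withdrawal ends assessment, the TAU comparisons set attenders against everyone. For recurrence, group-arm patients withdrawn for absence would also be observed for less time, so fewer of their later episodes could be counted, even if non-attenders do no worse.

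**Working it through.** **Inputs from the article.** N = 140 (Subjects), allocation 2:2:1, eight sessions in each programme (Intervention), two-sided 0.05 (Data analysis). Arms: 140 × 2/5 = 56, 56, and 140/5 = 28. The article gives no dropout rate, SD or effect size, so there is no stated figure to reproduce. Those used below are assumptions, shown over a range.

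**1. Bias against TAU from the absence rule (no true effect).** Let *w* be the share of a group arm withdrawn for absence and *g* the number of HDRS points by which their mean change is worse than that of attenders. Whole-arm mean = attenders' mean + *w* × *g*. TAU keeps its equivalent patients, so the complete-case difference is shifted by *w* × *g* towards the group arm.

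| *w* | *g* = 0 | *g* = 2 | *g* = 4 |
|---|---|---|---|
| 5% | 0 | 0.1 | 0.2 |
| 10% | 0 | 0.2 | 0.4 |
| 20% | 0 | 0.4 | 0.8 |
| 30% | 0 | 0.6 | 1.2 |

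**2. Type I error, group arm v TAU.** Null simulation, 56 v 28, 5,000 runs per setting. Assumed: SD of change 5; the same latent share of would-be non-attenders in every arm; 10% removed from every arm for clinical events, with change 5 points worse.

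| *w*, *g* | Simulated bias (points) | Complete cases | Everyone assessed |
|---|---|---|---|
| 10%, 2 | 0.22 | 5.2% | 4.7% |
| 20%, 2 | 0.40 | 6.2% | 5.0% |
| 20%, 4 | 0.75 | 9.5% | 5.3% |
| 30%, 4 | 1.21 | 14.3% | 4.5% |

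The Monte Carlo standard error at 5% is √(0.05 × 0.95 / 5000) = 0.3 percentage points, so the first row does not differ from nominal.

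**3. MBCT v psychoeducation.** Both arms carry the same rule, so the shift is *w*₁*g*₁ − *w*₂*g*₂, which is zero when the two are equal. The simulation (56 v 56, equal removal) gives bias near 0 and type I error of 4.6-5.1%. A shift needs unequal absence or unequal prognosis. For example, 20% v 10% at *g* = 4 gives 0.8 − 0.4 = 0.4 points towards the arm losing more.

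**4. Power at 0.5 SD.** Power = Φ(0.5/√(1/n₁ + 1/n₂) − 1.96).

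| Loss per group arm | n per group arm | MBCT v psychoeducation | Group arm v TAU (28 kept) |
|---|---|---|---|
| 0% | 56 | 75% | 58% |
| 10% | 50.4 | 71% | 56% |
| 20% | 44.8 | 66% | 55% |
| 30% | 39.2 | 60% | 52% |

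**5. If week 24 is entered in the model that supplies the primary test.** Suppose a share is lost by week 8 and the same share of the remainder by week 24. At 10%: 140 × 0.9 = 126 have a week-8 HDRS and 126 × 0.9 = 113 are analysed. At 15%: 119 and 101. At 20%: 112 and 90. If only V0 and V1 are entered, this further loss does not occur.

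**The case against.** The strongest reply is that the article nowhere says withdrawn patients stop being assessed. It says that all three groups are assessed at each visit and claims intention to treat. Follow-up after withdrawal and missing-data handling may be in the full protocol or analysis plan, which are not shown. This stands against any claim that intention to treat is impossible here. It does not remove the point, because the article does fix the withdrawal list and a complete-case model, and nothing shown reconciles them with the analysis set.

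Several stronger readings are tempting, and the document does not support them:

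- *The design favours MBCT.* The bias runs towards the group arms only against TAU, and for HDRS only if non-attenders do worse. The MBCT v psychoeducation aim is spared under equal removal.
- *Removing bad outcomes flatters the active arms.* The clinical-event rules apply in all arms and have no fixed direction. If such events were commoner in TAU, removing them would flatter TAU. Reaching HDRS ≥ 20 is not itself a listed withdrawal reason.
- *Recurrence contradicts withdrawal.* The episode or admission that triggers withdrawal has been observed and can be counted. What could be missed is recurrence after withdrawal for another reason.
- *A week-8 value is lost whenever week 24 is missing.* That holds only if week 24 is entered, which Data analysis does not settle.
- *The attendance rules conflict.* Intervention says "Attendance to at least 80% of the sessions of both interventions will be required to be considered complete": 0.80 × 8 = 6.4, so seven sessions. Withdrawal starts at the third unjustified absence. A patient attending six of eight (75%) is simply a retained non-completer, since the two rules serve different purposes.

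It is also fair to say that a mixed model assumes data missing at random, so it would not by itself cure outcome-dependent loss.

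**Conclusion.** The point holds as a gap between the stated analysis set and the rules meant to deliver it. If withdrawn patients leave assessment, the TAU comparisons become complete-case comparisons with loss that depends on arm. The shift towards the group arm is 0 to about 1.2 HDRS points, and the simulated type I error is 5.2-14.3% over the four settings tried. Both rest on assumed removal shares, prognosis gaps, SD and event rate. The main comparison mostly loses power, and group-arm recurrence after withdrawal for absence goes uncounted. If withdrawn patients are in fact still assessed, most of this disappears and the article needs only to say so. The trial calls itself a pilot meant to give preliminary effect sizes. That lowers the weight of the type I error but not that of a biased estimate.

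**What to change.** 1. **Withdrawal criteria.** Leave the listed reasons as they are. State that they end the study intervention only, and that every randomised patient who has not withdrawn consent is still assessed at V1 and V2 and followed for recurrence, whichever arm they are in.
2. **Data analysis.** Replace the repeated-measures ANOVA with a likelihood-based linear mixed model for repeated measures (arm × visit, unstructured covariance) using all observed visits of all randomised patients, with the week-8 contrast as primary.
3. **Sensitivity.** Add an analysis for data not missing at random, for example one that makes the unobserved change after withdrawal progressively worse, by arm.

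The cost is some follow-up visits after the intervention has stopped, a different SPSS procedure and a little more analysis work. No extra patients are needed. The first step has to be settled before patients reach V1, because missed assessments cannot be recovered later.

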### Primary outcome measures

Primary endpoint of the study is given by changes in the overall score of the Hamilton Rating Scale for Depression (HDRS [44]), from baseline (V0) to week 8 (v1) for each of the treatment groups.

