**Methods/design:**

A randomized, multicenter, prospective, versus active comparator, evaluator-blinded clinical trial is proposed. Patients with BD and subclinical or mild depressive symptoms will be randomly allocated to: 1) MBCT added to psychopharmacological treatment; 2) a brief structured group psychoeducational intervention added to psychopharmacological treatment; 3) standard clinical management, including psychopharmacological treatment. Assessments will be conducted at screening, baseline, post-intervention (8 weeks) and 4 month follow-up post-intervention. The aim is to compare MBCT intervention *versus* a brief structured group psychoeducation. Our hypothesis is that MBCT will be more effective in reducing the subsyndromal depressive symptoms and will improve cognitive performance to a higher degree than the psychoeducational treatment. It is also hypothesized that a significant increase of BDNF levels will be found after the MBCT intervention.

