The brain -derived neurotrophic factor (BDNF) is a dimeric protein that promotes the growth and maintenance of neuronal connections, modulates neurotransmission and participates in the mechanisms of learning and long-term plasticity (LTP). Peripheral BDNF in serum and plasma can be assessed noninvasively by venipuncture. Since it crosses the blood–brain barrier, its levels in serum and plasma are highly correlated with levels in cerebrospinal fluid (r ¼ 0.8) [37,38]. There are numerous studies assessing peripheral levels of BDNF in bipolar disorder patients. Some studies suggest that BDNF levels decrease during mood acute states and remain normal during euthymia, but other studies have contradicted this paradigm. A recent meta-analysis has measured the effect sizes of the differences in BDNF levels between BD patients in different mood states and controls. The BDNF levels were decreased in both mania and depression when compared to controls [39,40] but were not different in euthymia [41]. Meta-regression analyses in euthymia showed that age and length of illness influenced the variation in effect sizes [42]). BDNF levels are consistently reduced during manic and depressive episodes and recover after treatment for acute mania, so peripheral BDNF could be used as a biomarker of mood states and disease progression for BD.

In summary, the presence of persistent depressive subthreshold symptoms increases the risk of affective relapse and negatively affects the prognosis of BD. However, there is no an evidence-based specific treatment for them. MBCT appears as a promising intervention, since it has been found to be effective in reducing current depressive symptoms in MDD [23,43]. Our objective is to evaluate the efficacy of the MBCT added to standard drug treatment -following the recommendations of the Spanish Guideline for the Treatment of BD [11])- *versus* structured group psychoeducation versus standard clinical management. Our primary outcome is reduction of residual depressive symptoms. Secondary outcomes are manic and anxiety symptoms, recurrence, cognitive and social functioning and levels of BDNF.

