## Discussion

This study will provide feasibility information and preliminary effect size estimates to inform the effectiveness of adjunctive MBCT, adjunctive group psychoeducation and standard treatment on SS or mild depressive symptoms in BD. It is of interest to researchers involved in the development of new approaches to the treatment of residual affective symptoms and its negative impact in the course of illness. It can also provide information on variations of BDNF in the different treatment arms and on neuropsychological measures, which might suggest mechanisms of action and differences among treatments.

Strengths of the study include targeting a defined sample of bipolar patients with persistent depressive symptoms despite receiving a correct pharmacological treatment. This sample –as reported before- is representative of a high percentage of bipolar out-patients, who remain symptomatic more than one third of the time. The trial protocol was registered before randomization began (ClinicalTrials.gov: NCT02133170 Registered 04/30/2014) and was developed according to good clinical research practice enabling the randomized trial to be conducted with low risk of bias and a high degree of external validity. Both MBCT and psychoeducational interventions will be conducted using manuals and adherence to the treatment manuals will be tested. This makes it possible to implement the interventions in clinical practice, and the two interventions can be assessed in future trials. To standardize the application of MBCT and psychoeducation, specific training and meetings will be held. Specific training also may increase the inter-rater reliability on scales.

Since an 8-week psychoeducational program based in the Barcelona group-structured model has not proved effective neither in depressive symptoms nor in episode prevention, this could be a study weakness. But our objective is to compare MBCT versus an active psychosocial intervention, and this is the best model we could find. Sample size could also be a limitation, as well as the time of follow-up, especially regarding the possible effects on long-term course of BD.

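### The stated question is MBCT versus psychoeducation, but the primary endpoint is worded per arm and its three-arm repeated-measures ANOVA has no deciding contrast.

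*Protocol article*

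**What the plan says.** - **Aim and hypothesis** (abstract, Methods/design): the superiority hypothesis reads: "MBCT will be more effective in reducing the subsyndromal depressive symptoms and will improve cognitive performance to a higher degree than the psychoeducational treatment". The Discussion repeats the pairwise aim: "But our objective is to compare MBCT versus an active psychosocial intervention".
- **Objective in the Background**: this is three-way, with MBCT set against "structured group psychoeducation versus standard clinical management".
- **Primary endpoint** (Primary outcome measures): HDRS change "from baseline (V0) to week 8 (v1) for each of the treatment groups". No difference between arms is named.
- **Analysis** (Data analysis): change in primary and secondary outcomes is analysed with a general linear model, described as ANOVA with repeated measures. No model term or contrast is named. The section also lists t-test, Mann-Whitney, Kruskal-Wallis and ANOVA as generic choices that depend on normality. It ends: "The statistical package SPSS 18.0 is used in all tests and a bilateral level of p < 0.05 is considered statistically significant".
- **BDNF** (abstract, Methods/design): the hypothesis is that "a significant increase of BDNF levels will be found after the MBCT intervention", a before-after statement about one arm.
- **Design** (Methods/design; Subjects): three arms, allocation 2:2:1, 140 patients, assessed at baseline, week 8 and six months.
- **Status** (Discussion): "This study will provide feasibility information and preliminary effect size estimates".

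**The concern.** The trial asks a question about two arms, but the endpoint and the method assigned to it do not point to that question. The endpoint can be reported arm by arm. The method, in a three-arm trial, naturally yields an omnibus group-by-time test, which responds to any difference among the arms. If all visits are in the model, it also responds to differences that appear only at the later visit.

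Two things are at stake. First, a significant primary result could be driven by TAU and still be read as support for MBCT over psychoeducation. Second, if MBCT really is better at week 8, spreading the test over arms and visits can cost power for the one comparison the trial was set up to make.

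**Working it through.** **Inputs from the article.** N = 140 at 2:2:1 gives 140 × 2/5 = 56, 56, and 140 × 1/5 = 28. Three visits; two-sided 0.05. The article states no effect size, SD, power or dropout, so 140 cannot be reproduced as a power calculation.

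**Assumptions.** HDRS SD = 1 at each visit, equal between-visit correlation ρ = 0.3 to 0.5, no dropout. Effects are in SD units.

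**Scenario A: MBCT = psychoeducation, both 0.6 SD better than TAU at both later visits.**
- Mean benefit over all patients: 0.6 × 112/140 = 0.48. Deviations: 0.12 in the active arms, -0.48 in TAU.
- Σ n × deviation² = 112 × 0.0144 + 28 × 0.2304 = 8.064.
- Three visits: the time pattern (0, 1, 1) has centred sum of squares 2/3. Noncentrality = 8.064 × (2/3)/(1-ρ) = 7.68 at ρ = 0.3 and 10.75 at ρ = 0.5. With F on 4 and 274 df, the probability of significance is 58% and 74%. Simulation gives 57-74%.
- Two visits: the pattern (0, 1) has centred sum of squares 1/2. Noncentrality = 8.064 × (1/2)/(1-ρ) = 5.76 and 8.06. With F on 2 and 137 df this gives 56% and 71%. Simulation gives 56-71%.
- Direct MBCT-psychoeducation test at week 8: about 5%, as it should be.

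**Scenario B: MBCT better by 0.5 SD at week 8 and 0.2 SD at week 24; psychoeducation = TAU.**
- Arm factor: 56 × 84/140 = 33.6. The time pattern (0, 0.5, 0.2) has mean 0.233 and centred sum of squares 0.1267.
- Three-visit group-by-time: noncentrality = 33.6 × 0.1267/(1-ρ) = 6.08 and 8.51, so power is 47% and 63%. Simulation gives 48-63%.
- Direct contrast, 56 v 56: power = Φ(0.5/σ × √28 - 1.96).

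| Analysis | σ at ρ = 0.3, 0.5 | Power by formula | Simulated |
|---|---|---|---|
| Unadjusted change, σ = √(2(1-ρ)) | 1.183, 1.000 | 61%, 75% | 62-75% |
| Baseline-adjusted, σ = √(1-ρ²) | 0.954, 0.866 | 79%, 86% | 79-85% |

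Formula and simulation agree to within about one percentage point.

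**Where the power loss comes from.** Part of the gap is choice of contrast and part is baseline adjustment. At ρ = 0.3 the step from omnibus to unadjusted contrast is 48 to 62, and adjustment takes it from 62 to 79. The first step also depends on the effect fading. If MBCT stays 0.5 SD better than both other arms at week 24, the three-visit test has 60-76% power against 60-75% for the unadjusted contrast, so nothing is lost there. A two-visit omnibus test of week-8 change has 58-73% in that case.

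**Single contrast.** Type I error is 5% by construction. Power is 80% at a standardised difference of (1.96 + 0.84) × √(2/56) = 0.53 SD of the analysed quantity, before dropout.

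**The case against.** The strongest reply is that the endpoint sentence defines a variable measured in every arm, not a test, and that the comparison is plain from the abstract and the Discussion. Between-group t-tests are listed in Data analysis, an unseen analysis plan may name the contrast, and the trial is labelled a pilot.

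Much of this stands, and it rules out several stronger readings that a reader might infer:
- *That within-arm tests decide efficacy.* No section says so. An argument from regression to the mean after selection on HDRS would therefore attack an inference the article does not state. The abstract also lists separate screening and baseline assessments, which would weaken that effect if HDRS is measured again.
- *That a three-arm, three-visit interaction is the fixed decision rule.* This is a reading. The primary endpoint stops at week 8 and week 24 sits under Secondary endpoints, so a two-visit model fits equally well. Scenario A shows that the problem remains with two visits.
- *That 0.05 is claimed separately for all tests, with a long list of false positives to be counted.* The words about all tests belong to the software package. The article does not prescribe pairwise tests of every outcome, and adjustment for multiplicity is commonly left to the analysis plan.
- *That the Scenario A figures are false claims for MBCT.* TAU really differs there, and the Background includes TAU in the objective. If the omnibus test is followed by the direct contrast, a false claim of MBCT superiority arises in about 5% of trials.

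What the reply does not remove is the mismatch in the printed text. The generic t-tests are not attached to the primary endpoint, whereas the repeated-measures ANOVA is. Pilot status softens the consequence, but the article still states a superiority hypothesis and a significance level.

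**Conclusion.** The point holds as a mismatch between the stated question and the printed primary endpoint and analysis, not as a complaint about detail absent from an article. A significant omnibus group-by-time result would not by itself answer the MBCT-psychoeducation question. Under the assumptions of Scenario A it occurs in about 57-74% of trials with three visits and 56-71% with two, although the two arms are equal, against about 5% for the direct contrast.

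The power cost is real but conditional. It is 48-63% against 62-75% (unadjusted) or 79-85% (baseline-adjusted) when the effect fades by week 24. When the effect persists, only the baseline adjustment brings a gain. All these sizes rest on assumed effects, a correlation of 0.3 to 0.5 and complete data, because the article gives no figures of its own.

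**What to change.** Reword Primary outcome measures and Data analysis in the protocol article along these lines:

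- Primary analysis: the single MBCT minus psychoeducation difference in HDRS at week 8, adjusted for baseline HDRS (ANCOVA or the equivalent contrast from a longitudinal model), tested at two-sided 5% and reported with a 95% confidence interval.
- Secondary: MBCT versus TAU, psychoeducation versus TAU, and all week-24 comparisons.
- Efficacy conclusions rest on differences between arms. Restate the BDNF hypothesis in the abstract as a between-arm difference.
- Align the three-way objective in the Background with the pairwise aim in the abstract and Discussion.

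Name the baseline adjustment explicitly. Without it, the contrast has the unadjusted power, not the 79-85%.

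The cost is wording only, with no extra patients or visits. The downside is that an omnibus or TAU-driven result can no longer count as the primary finding.
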